## Abstract

**Background:**

E-cigarette use (i.e., vaping) is prevalent among young adults in the U.S. Studies show that young adults who vape are more likely to initiate cigarette smoking than young adults who do not vape. Despite this, little research on vaping interventions and prevention of smoking for young adults who vape exist.

**Methods:**

A 2-arm pilot randomized controlled trial (RCT) will be conducted by recruiting young adults ages 18–24 who reported vaping at least once per week in the past 30 days and having never smoked cigarettes at baseline. Participants will be recruited via social media ads and be randomly assigned to an intervention arm, which will be the Live Free From E-cigarettes (LIFFE) mobile-based program (*n* = 50), or a waitlist control arm (*n* = 50). The primary outcomes are biochemically verified 7-day point prevalence abstinence for nicotine vaping, vaping reduction, and smoking susceptibility. Outcomes are measured at 2-, 4-, and 8-weeks after randomization.

**Discussion:**

This is the first RCT to evaluate the effectiveness of a mobile-based intervention that targets smoking susceptibility while also supporting vaping cessation or vaping reduction in young adults. Findings may inform future efforts to prevent transition to cigarette smoking and vaping cessation and reduction in young adults.

**Trial registration:**

ClinicalTrials.gov: NCT06129123; Date of registration: 11/10/2023.

## Background

E-cigarette use, colloquially known as “vaping,” presents a public health concern among young adults (ages 18–24), with the most recent numbers indicating that 10.3% and 15.5% reported current use among those ages 18–20 and 21–24, respectively [1]. These high rates of vaping among young adults are particularly concerning given that long-term health effects of vaping (especially as compared to the effects of combustible cigarettes) are currently not largely understood; however, emerging research and case studies have pointed to potential risks for respiratory, cardiovascular, pulmonary, and oral health issues [2–6]. Young individuals who vape are also at risk for the long-term negative effects that nicotine can have on cognition and neural development, including permanent epigenetic changes in the genome that can be passed to subsequent generations [7]. Nevertheless, young adult e-cigarette users perceive vaping to be of low risk, which may promote continued use [8, 9]. Importantly, vaping also serves as a gateway into combustible cigarette smoking [10–12], with a systematic review indicating consistent direct associations between vaping at baseline and smoking initiation and smoking progression during follow-up [13].

Despite high rates of e-cigarette use in this age group, several studies found that over half of young adult e-cigarette users want to quit vaping [14, 15]. A handful of brief and mobile-accessible interventions have thus been developed to prevent vaping and encourage abstinence from e-cigarettes in young adults [16–20]. For example, a program that delivered text messages over the course of nine weeks was shown to be effective for promoting vaping cessation among young adults [20]. Trials of other programs, such as an app-based intervention [21] and an Instagram-based program are underway [17]. However, additional evidence-based interventions—especially those developed with feedback and qualitative data from young adults—are needed, especially those which address the transition from vaping to smoking combustible cigarettes. At present, there are no known evidence-based treatments that target this phenomenon.

Qualitative research conducted with young adults who vape can provide key information on how to effectively target e-cigarette use. Young adults have responded well to mobile interventions, showcasing promise for this mode of delivery [18–20, 22]. At present, there is limited research examining young adults’ beliefs about what should be included in mobile interventions that target e-cigarette use. However, one study among adolescents who vape found interest in education regarding the health effects of vaping, anecdotes from others who vape, and incentives for cessation [23]. Additionally, a qualitative study led by Tran et al. (2023) investigated young adults’ thoughts on intervention tools that can address vaping as well as the transition to combustible cigarettes [24]. Of note, participants endorsed the inclusions of peer support, cessation progress tracking, education about the harms of e-cigarettes, gamification, and incentivization. Young adults also believed that interventions should include education about the harms of combustible cigarette smoking, teach refusal skills for offers to smoke, and incorporate personal anecdotes from former smokers. It is important that interventions, if they are to be effective, include user feedback from young adults who vape and/or smoke cigarettes.

Personalized normative feedback (PNF) has exhibited promise as a tool for promoting alcohol cessation, including among young adults [25, 26]. Using the styles and techniques of motivational interviewing (MI), PNF helps individuals to reassess and change their behavior by addressing misperceptions of norms regarding said behavior. Although there is no research at present investigating PNF’s efficacy in vaping interventions among young adults, it may be particularly relevant given its emphasis on correcting misperceptions of norms and providing education on young adults’ rates and acceptance of e-cigarette use. Emerging research has indicated that young adult e-cigarette use is associated with their perceptions of their peers’ use and approval of use [27, 28], thus showing support for vaping interventions that address perceived norms.

## Objectives

In a pilot randomized controlled trial (RCT), the present study will test a brief, mobile-accessible intervention primarily built upon PNF to target vaping and the transition to smoking combustible cigarettes among young adults. The primary aim is to determine the efficacy of the program on reducing past 7-day vaping frequency and susceptibility to smoking and increasing biochemically verified 7-day point prevalence abstinence in the immediate term (2-weeks post-randomization) and short-term (4- and 8-weeks post-randomization).

## Methods/Design

### Trial design

This study is a 2-arm pilot RCT with 100 young adults who vape recruited through advertisements placed on social media. Participants will be randomized to the active intervention arm (*n* = 50) or to a waitlist-control arm (*n* = 50).

### Inclusion criteria

Participants are considered eligible if they: [1] are between the ages of 18–24; (b) are able to read English; [3] report vaping at least one day per week in the past month; and [4] report no history of cigarette use at screening and baseline. The inclusion criterion of vaping on at least one day per week in the past month was determined based on existing literature on other vaping intervention trials. Sanchez et al. (2023) and Graham et al. (2021) chose to include those who report using e-cigarettes in the past 30 days [20, 21]. Lyu et al. (2022) and Palmer et al. (2022) chose to include those who report vaping on at least one day per week in the past month and on at least 25 days per month, respectively [17, 18]. PATH data suggest potential low frequency of e-cigarette use, with young adults vaping on an average of 10 days in the past month [16]. Thus, we chose the most moderate inclusion criterion of vaping on at least one day per week.

### Exclusion criteria

Young adults who are currently receiving nicotine cessation services (e.g., counseling services, nicotine replacement therapies, quitline services, self-help materials, apps or other online supports for quitting vaping) will be excluded from the study. Those who report having been diagnosed with a serious mental illness (e.g., schizophrenia or schizoaffective disorder, bipolar disorder), having used an illicit drug in the past 30 days (e.g., cocaine, heroin), or screening positive for an alcohol use disorder in the past year will be ineligible, as they likely require a higher level of care.

### Recruitment and enrollment

Participants will be recruited through online advertisements that will be placed on social media platforms known to be frequented by young adults, such as Instagram and Reddit. Advertisements will briefly describe the study opportunity and include a link to the study’s website that will include a more detailed description of the study’s procedures. The link will also lead interested parties to our screening survey to preliminarily determine their eligibility. Those who are determined to be eligible via this screening survey will be contacted via phone by research personnel to confirm responses to ensure they are not falsifying information and review the consent form to confirm their understanding. Individuals who are considered eligible through both the screening survey and contact with a research team member will be sent a consent form to complete electronically.

### Informed consent

Following eligibility screening procedures, prospective participants must provide informed consent to be enrolled into the study. The electronic informed consent form will provide details about the requirements for participation, LIFFE intervention, voluntary nature of the study, potential risks associated with study participation, incentives, randomization process, and contact information for the study lead and university IRB. Participants will be notified that they may change their mind and discontinue their participation in the study at any time without penalty. After electronically signing the informed consent form, the baseline assessment will be immediately launched.

### Study procedure

After signing the consent form, participants will complete a 20-minute baseline survey. Upon completion of the baseline survey, all participants will receive a $25 gift card and be randomized to the intervention (*n* = 50) or the waitlist control condition (*n* = 50). We will utilize stratified randomization to ensure that an equal number of males and females are randomized into each condition. Those randomized into the intervention will be prompted by research personnel to complete the 30-minute intervention, which will be delivered via a webpage accessible through a mobile device. More specifically, participants will be emailed a web link to access the intervention along with personalized log-in information consisting of their email address and a unique 4-digit PIN code. We will collect backend data indicating whether participants have completed all intervention components. We anticipate that most or all participants will complete the intervention given the 100% completion rate in one sitting among those who beta tested our program (completed June 2024; *N* = 20). However, if there are participants who have not completed the full intervention within 24 h of being given access to the program, research personnel will send a text and email reminder. All participants will then complete brief surveys, which will include the same measures from the baseline survey, 2, 4-, and 8-weeks post-randomization (see Fig. 1), to determine the efficacy of the program on reducing vaping and susceptibility to smoking in the immediate term (2-weeks post-randomization) and short term (4- and 8-weeks post-randomization). At most, three text messages and three emails will be sent to remind participants to complete the assessments. Those who do not respond despite the reminder attempts are counted as dropout at each time point. However, participants who do not respond in the previous assessment waves will still be contacted for later assessments. For instance, a participant who did not complete the 2-week follow-up assessment will still be asked to complete the 4-week assessment. Participants will receive a $25 Amazon gift card for completing each survey (up to $100 total). Participants will also be offered raffle tickets for a chance to win various prizes (e.g., movie tickets, $50 Amazon gift card). More specifically, participants will receive one raffle ticket for each survey they complete within two days of receiving the survey via email, giving them the opportunity to earn up to four raffle tickets. Participants who complete all four surveys within two days of receiving them will earn an additional three raffle tickets.

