#### Covariates

Because the use of other tobacco products and substances are common in young adults [38–41], we will ask participants to report whether they have used other nicotine products (e.g., oral nicotine pouches, cigars, hookah), cannabis, and alcohol at baseline and follow-up timepoints. Those who indicate current use of other nicotine products (aside from combustible cigarettes) will not be excluded, as they may benefit from engaging in vaping cessation efforts. Additionally, because it is possible that participants may have initiated cigarette smoking during their participation in the study, we will also assess for cigarette use during our follow-up assessments.

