### Data analysis plan

#### Primary analysis

Treatment effects of the intervention will be examined using within-subjects repeated measures analysis of variance (RM-ANOVA), which allows for investigations of changes in mean scores over 3 or more time points. Specifically, we will evaluate two models to examine whether there were changes in past 7-day vaping frequency and smoking susceptibility across 3 time points (2-, 4-, and 8-weeks post-randomization) among those who completed the intervention. Logistic regression will be used to examine point prevalence abstinence at our 3 follow-up timepoints. Next, RM-ANOVA will be used to determine whether any changes in past 7-day vaping frequency and smoking susceptibility are the result of the interaction between the condition and time. Past 7-day point prevalence abstinence will be compared between the treatment and control groups using logistic regression. To handle missing data, we will conduct an intent-to-treat (ITT) analysis in which those who were lost to follow-up will be marked as treatment failures.

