#### Power analysis

Power analyses were performed with power = 0.8 and alpha = 0.05 for small (f = 0.15), moderate (f = 0.25), and large (f = 0.45) effect sizes. With 100 participants, we are adequately powered to detect small (*n* = 62), moderate (*n* = 24), and large (*n* = 10) effects. We anticipate small to medium effects based on previous studies using PNF [42–44].

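### The planned between-arm analyses use neither the sex stratifier nor the baseline value of the outcome, and the Covariates section does not limit adjustment to baseline measurements

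*Protocol article*

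**What the plan says.** All of this is in the protocol article.

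- **Study procedure.** Allocation is stratified by sex: "We will utilize stratified randomization to ensure that an equal number of males and females are randomized into each condition".
- **Baseline variables.** The baseline survey records the primary and secondary outcomes, including days vaped in the past week and smoking susceptibility. Baseline values are therefore available for every continuous primary outcome.
- **Primary outcomes.** The vaping outcome is framed as a reduction in past-week frequency, which presupposes a starting value.
- **Primary analysis.** Repeated-measures ANOVA is first described for intervention completers over the 2-, 4- and 8-week visits. It is then used for the condition-by-time interaction, with no other visit and no covariate named. For abstinence: "Past 7-day point prevalence abstinence will be compared between the treatment and control groups using logistic regression". No covariate is named there either.
- **Exploratory analysis.** Sex appears only as a possible moderator.
- **Covariates.** Other nicotine products are recorded, together with "cannabis, and alcohol at baseline and follow-up timepoints". Cigarette use is recorded at follow-up because "it is possible that participants may have initiated cigarette smoking during their participation in the study". The section does not say which of these variables enters which model, or at which time point.

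**The concern.** A factor used to stratify allocation should normally appear in the model that compares the arms, so that the standard error reflects the design. The baseline value of a continuous outcome is usually its best predictor. Eligibility here runs from vaping on one day a week upwards, so participants should start far apart. With 50 per arm, ignoring a measured baseline gives up precision and leaves chance imbalance in starting level uncorrected.

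The Covariates section raises a second issue. It is the only place where adjustment variables are listed, and it mixes baseline with follow-up measurements. Follow-up substance use, and new cigarette use in particular, comes after randomisation and may be changed by the intervention. An analyst who took the heading literally could remove part of the effect under study.

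**Working it through.** **1. The plan's own figure.** The Power analysis section uses "power = 0.8 and alpha = 0.05" and concludes: "With 100 participants, we are adequately powered to detect small (*n* = 62), moderate (*n* = 24), and large (*n* = 10) effects". Take the noncentral F for a within-subject or interaction effect, with noncentrality f²·N·m/(1 − ρ) and degrees of freedom (k − 1)(m − 1) and (N − k)(m − 1). Set k = 2 arms, m = 4 measurements, ρ = 0.5 and sphericity; m, ρ and sphericity are assumptions, as the section does not state them.

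- f = 0.15, N = 62: 0.0225 × 62 × 4 / 0.5 = 11.16, power 0.801.
- f = 0.25, N = 24: 0.0625 × 24 × 4 / 0.5 = 12.0, power 0.816.
- f = 0.45, N = 10: 0.2025 × 10 × 4 / 0.5 = 16.2, power 0.89.

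The figures 62, 24 and 10 reproduce exactly. With m = 3 the requirement is 74, 28 and 10, still below 100. This calculation is for a within-person test, so it does not size an arm comparison at a visit.

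**2. Baseline adjustment, one visit.** Adjusting for a baseline with correlation ρ leaves 1 − ρ² of the variance. The equivalent sample-size factor is 1/(1 − ρ²). The detectable difference at N = 100, two-sided 5% (an assumption) and 80% power is 2.80·√(4(1 − ρ²)/100) SD. Unadjusted, it is 2.80 × 0.2 = 0.560.

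| ρ (assumed) | Variance left | Sample-size factor | Detectable difference |
|---|---|---|---|
| 0.3 | 0.91 | 1.10 | 0.534 SD |
| 0.5 | 0.75 | 1.33 | 0.485 SD |
| 0.7 | 0.51 | 1.96 | 0.400 SD |

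**3. Baseline adjustment, mean of three visits.** Under compound symmetry the variance is (1 + 2ρ)/3 unadjusted and (1 + 2ρ)/3 − ρ² adjusted. Power is for a difference of 0.3 SD with 50 per arm.

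| ρ (assumed) | Unadjusted | Adjusted | Ratio | Power |
|---|---|---|---|---|
| 0.3 | 0.533 | 0.443 | 0.83 | 0.54 to 0.62 |
| 0.5 | 0.667 | 0.417 | 0.63 | 0.45 to 0.64 |
| 0.7 | 0.800 | 0.310 | 0.39 | 0.39 to 0.77 |

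**4. The condition-by-time interaction.** This test uses differences between follow-up visits. Under compound symmetry Cov(Yj − Yk, Y0) = ρ − ρ = 0, in SD² units, so a baseline covariate gives it no precision. The gains in steps 2 and 3 need an arm contrast at a visit or averaged over visits.

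**5. Sex.** Simulation: 8,000 runs, 100 participants, 25 in each sex-by-arm cell, within-sex SD of 1.

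| Sex difference | Type I error without sex | Power at 0.5 SD without sex | Power with sex |
|---|---|---|---|
| 0 | 0.053 | 0.69 | 0.70 |
| 0.3 SD | 0.045 | 0.69 | 0.70 |
| 0.6 SD | 0.043 | 0.66 | 0.69 |
| 1.0 SD | 0.026 | 0.61 | 0.69 |

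Omitting sex makes the test conservative, and the loss is small unless the sexes differ greatly.

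**6. Adjusting for follow-up smoking, if it were done.** Simulation of 400,000 with an assumed direct effect of −0.3 SD and an assumed effect of smoking on the outcome of 1 SD. Initiation rates are nominal.

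- 10% v 5%: total effect −0.346, adjusted −0.295 (15% smaller). With an unmeasured shared cause: −0.366 to −0.277 (24%).
- 20% v 10%: −0.403 to −0.303 (25%). With a shared cause: −0.408 to −0.255 (38%).

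**The case against.** An article may leave its covariate list to the analysis plan, and the Primary analysis section never says that the models are unadjusted. That stands in part: an unseen plan may already hold these terms. What the article does print is the visits and the comparisons, and neither sex nor a baseline value is among them. If baseline were entered as a fourth time point, the comparison would act on change from baseline. For the three-visit mean at ρ of 0.3, 0.5 and 0.7, that has variance 0.933, 0.667 and 0.400, against 0.443, 0.417 and 0.310 with baseline as a covariate.

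The objection that the variance gain does not fit the named tests is right. It does not apply to the interaction (step 4). Nor does it carry over to logistic regression: there, a prognostic covariate generally raises power without shrinking the standard error of the log odds ratio, and the odds ratio becomes conditional rather than marginal.

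A reader might infer that the plan adjusts for post-randomisation variables. It does not say so. The Covariates section names baseline as well as follow-up values for other nicotine, cannabis and alcohol, and for cigarettes it describes only assessment. A reader might also infer that a trial outcome is being used as a covariate. Cigarette initiation is not a listed primary or secondary outcome; the smoking outcomes are susceptibility, perceived harms and motivation to initiate. It is a post-randomisation event that the intervention aims to affect, which is reason enough not to adjust for it.

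**Conclusion.** The point holds as an avoidable loss of precision and an unclear covariate rule. It does not make the randomised comparison invalid.

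- **Baseline value: the material part.** For a single-visit continuous comparison, 9% to 49% of the variance is removable at assumed correlations of 0.3 to 0.7. At 0.5 the detectable difference falls from 0.56 to about 0.49 SD. For the three-visit mean, under compound symmetry as well, 17% to 61% is removable. The documents supply no correlation, so these are ranges and not estimates for this trial.
- **Sex: minor.** A reader might infer that leaving out the stratifier inflates false positives. The check shows the reverse: the test becomes conservative.
- **Follow-up covariates: conditional.** Bias arises only if such values are used. The 15% to 38% attenuation illustrates assumed scenarios and is not a forecast.

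**What to change.** 1. **Continuous outcomes.** Include sex and the baseline value of the same outcome in the between-arm models. Estimate the arm difference at each follow-up visit or averaged over visits, because the interaction alone does not gain from baseline.
2. **Abstinence.** Include sex and baseline past-7-day vaping days in the logistic model, and state that the odds ratio is then conditional on them.
3. **Covariates section.** State that only baseline values of other nicotine, cannabis and alcohol use may serve as adjusters.
4. **Cigarette use during follow-up.** Report it by arm and keep it out of the adjustment set.

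The cost is analysis-plan wording. Every variable is already collected; no visit, measure or participant is added. The wording should be fixed before outcome data are examined by arm.

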
**Fig. 1 Fig1:**
[figure not shown]
Participant flow of the randomized controlled trial

### Development of the intervention

The intervention is called LIFFE (Live Free From E-Cigarettes), which is a 30-minute mobile-accessible interactive program that is personalized to the participant’s individual vaping behavior and beliefs (based on the baseline surveys). Using an iterative process, LIFFE was developed based on evidence supporting PNF and MI in addressing substance use behaviors [25, 29, 30] and recommended best practices for addressing tobacco use and dependence [31]. The first version of LIFFE was informed by our previous qualitative work through a series of focus groups with young adults who vaped, formerly vaped, or vaped and transitioned to smoking [24]. Where possible, we included intervention components that were identified as preferred by young adults who vape, such as teaching participants alternative ways to manage stress, to solicit peer support during quit attempts, and to track their progress with quitting.

The intervention also contains PNF, MI, and education about vaping and smoking harms. The program begins with the MI-based portion, which includes exploration of their experienced health and personal consequences of vaping and potential reasons for and motivation for shifting vaping behaviors (e.g., to save money, to be free from addiction). Drawing on relational methods of MI, the intervention is presented in ways that assume that users know the options that are best for themselves (i.e., “The decision is yours!”) with content that is written in empathetic and encouraging language. We intend to evoke relatedness by building an alliance with the user by also providing opportunities for exploration of options and self-reflection. The intervention will help users to identify reasons, abilities, and opportunities for behavior change (“What are some negatives you have personally experienced since you started vaping?”) and produce change talk (“On a scale from 1–10, with 10 being the highest, how ready [or important or confident] are you to reduce or quit vaping?”). These MI-based content will be used to help move individuals from not considering changing their vaping to considering taking action toward behavior change.

Second, the education portion involves presentation of the actual harms posed by e-cigarettes to clarify any misperceptions of the negative effects of vaping and nicotine exposure in young adults. To address our goal of decreasing susceptibility to smoking, education about the harms of smoking were also included. Based on focus groups with young adults with vaping histories, the education portion included the long-term harms of smoking but especially highlighted the more immediate harms of smoking, which participants reported as more relevant to their age group [24].

Next, users are presented with the PNF portion. In the PNF portion, participants receive feedback about their perceptions of peer vaping by presenting their typical behavior/attitude alongside their perceptions of others’ behavior/attitude alongside the actual norm of the behavior/attitude obtained from the Happiness and Health Study (H&H Study), which comprises of longitudinal cohort data from over 2200 young adults. For example, a participant may see descriptive norms feedback such as “You thought that 40% of people vaped in the past 30 days.” They will then be presented with a figure showing that based on recent research of over 2200 young people, 76.8% of young adult men and 83.6% of young adult women did not vape at all. They will also see that only 4.6% of men and 4.4% of women approve of vaping. Smoking-related normative data are also presented, such as only 2.5% of men and 1.3% of women approve of smoking cigarettes. A brief description of the normative data source (H&H sample) will be provided, which will include the diversity of the sample and help increase believability of the data.

Lastly, strategies recommended for nicotine cessation are presented. For example, in addition the strategies listed previously (e.g., teaching participants alternative ways to manage stress, to solicit peer support during quit attempts, and to track their progress with quitting), participants are taught to select a quit date, identify triggers of their vaping, create incentives for their progress with quitting, and other ways to prepare to quit (e.g., dispose of all vaping-related items prior to quit date). Video testimonials from young adults who formerly vaped, are in the process of quitting, are considering quitting, or vaped and transitioned to smoking are included with tips based on their personal lived experiences with vaping and quitting.

Beta testing of this initial version was recently completed (June 2024) with 20 young adults who reported currently vaping. Using a mixed methods design, both quantitative measures and interviews were used to elicit feedback on the feasibility and acceptability of the program as well as suggestions for improvement. Themes from these interviews have been identified, which will inform the next version of LIFFE for the RCT. Suggested modifications for further improvement, which are being addressed during intervention refinement prior to the RCT, include decreasing the large chunks of texts, having more interactive features (e.g., pop quizzes, ‘check your knowledge’ questions), and having a specific place for users who are motivated to quit to select a quit date (e.g., calendar). Other suggestions that are not feasible to address prior to this pilot RCT will be addressed prior to a subsequent larger RCT, which include having “booster sessions a month or a few months later,” giving users the opportunity to review content and strategies presented during the first session.

